#### Statistical analysis

A comparison of continuous outcome measures between ARC and SMC infusions, such as the mean T/N activity concentration and mean decrease in total lesion glycolysis at 3 months posttreatment, will be performed by means of a paired *t* test. Categorical outcome measures, such as infusion efficiency and disease control rates at 3 months posttreatment, will be compared with a McNemar’s test. The value of the ^166^Ho scout dose distribution will be assessed per catheter type. Correlation and agreement with the ^166^Ho therapy dose distribution will be evaluated with a linear regression analysis (R^2^) and Bland-Altman analysis (limits of agreement), respectively. The dose-response relationship will be evaluated by linear regression analysis. Survival analysis by the Kaplan-Meier method will be used to estimate the median overall survival time for the entire cohort. The primary analyses will be performed on an intention-to-treat (as randomized) basis.

A two-sided *p* value < 0.05 will be considered statistically significant.

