### Study objectives

The primary objective is to assess the difference in posttreatment T/N activity ratio on SPECT/CT between administration with the ARC and SMC.

Secondary objectives include comparison of the following endpoints between administrations with the ARC and SMC: mean tumor and healthy liver absorbed dose on SPECT/CT, percentage of calculated treatment activity administered (infusion efficiency), predictive value of the ^166^Ho scout dose distribution, and posttreatment tumor response. Furthermore, the presence of a dose-response relation between tumor absorbed dose and posttreatment tumor response will be evaluated.

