### Outcome assessment

In every target vessels’ perfusion territory, the absorbed dose on ^166^Ho-SPECT reconstructions will be determined for the metastases and the healthy liver tissue [4]. Consequently, a posttreatment T/N activity ratio will be calculated for each perfusion territory by dividing the number of counts in tumorous and healthy liver tissue.

The predictive value of the scout dose will be assessed by comparison of the distribution of the scout dose with the treatment dose. The analysis will be based on tumor and healthy liver absorbed doses on SPECT/CT analysis.

Infusion efficiency is defined as the percentage of the prepared treatment activity that is infused. The ^166^Ho activity that is not infused will be determined by measuring the administration system (vial, lines, and catheters) with a dose calibrator.

Response analysis will be performed in accordance with the Response Evaluation Criteria in Solid Tumors (RECIST) version 1.1 [12], for each functional liver lobe separately. Disease control rates (percentage of liver lobes with complete response, partial response or stable disease) will be determined by CT evaluation at 3 months posttreatment. Metabolic tumor response will be determined by assessing the change (relative to baseline) in total lesion glycolysis values on ^18^F-FDG-PET imaging. During the response assessment, observers will be blinded for the catheter type used.

The relationship between tumor absorbed dose on SPECT/CT and tumor response on both CT and ^18^F-FDG-PET will be characterized on the level of perfusion territories.

Common Terminology Criteria for Adverse Events v 4.03 will be used to describe laboratory and clinical toxicity for the entire cohort, with specific attention for device-related adverse events per catheter type such as the occurrence of reflux, vasospasm, or arterial dissections.

The municipal administration will be consulted to assess the overall survival, measured from treatment onward.

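### Infusion efficiency is defined as a measured percentage but is classed as categorical and assigned to McNemar's test, with no cut-off given

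*Protocol article*

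**What the plan says.** All references are to the protocol article.

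- **Role.** Study objectives: "Secondary objectives include comparison of the following endpoints between administrations with the ARC and SMC". Infusion efficiency is on that list, described as "percentage of calculated treatment activity administered (infusion efficiency").
- **Definition.** Outcome assessment: "Infusion efficiency is defined as the percentage of the prepared treatment activity that is infused".
- **Measurement.** The same section adds that the "activity that is not infused will be determined by measuring the administration system (vial, lines, and catheters) with a dose calibrator".
- **Analysis class and test.** Statistical analysis: "Categorical outcome measures, such as infusion efficiency and disease control rates at 3 months posttreatment" "will be compared with a McNemar’s test".
- **The alternative class.** The sentence before that one covers the other kind of outcome: "A comparison of continuous outcome measures between ARC and SMC infusions" is to use a paired t test.
- **The other outcome given to McNemar's test.** Outcome assessment defines the disease control rate as the "percentage of liver lobes with complete response, partial response or stable disease".

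The article states no cut-off, category or success criterion for infusion efficiency.

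**The concern.** A dose-calibrator reading gives one number on a continuous scale for each infusion, so each patient contributes a pair of percentages, one per catheter. McNemar's test takes a pair of yes/no results. The analysis section therefore names a test that the endpoint, as defined a few paragraphs earlier, does not supply with data.

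A named comparison between the catheters is at stake. Raising infusion efficiency is one of the aims that the Background gives for the anti-reflux catheter, and the abstract lists it as a secondary endpoint. If the analysis section is followed literally, someone must choose a threshold before the test can be run. The choice affects both how much information survives and what the result is.

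**Working it through.** **1. Does any figure in the plan depend on this endpoint?** The plan gives no expected value, spread or power for infusion efficiency. Its only sample size is for the T/N ratio (difference 0.4, SD 0.57, two-sided alpha 0.05, power 0.90, stated minimum 23). Taking 0.57 as the SD of the within-patient difference:

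- Normal approximation: ((1.960 + 1.282) × 0.57 / 0.4)² = 21.3, so 22.
- Exact noncentral t: 24 (power 0.895 at 23, 0.908 at 24, 0.920 at 25).

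The stated 23 lies between the two. Infusion efficiency is not an input, so the sample size does not bear on this point.

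**2. The two percentages side by side.**

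| Outcome | Percentage of what | Value per lobe | Class in the plan | Fit |
|---|---|---|---|---|
| Disease control | lobes | yes / no | categorical, McNemar | fits |
| Infusion efficiency | activity within one infusion | a number, in % | categorical, McNemar | does not fit |

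Both are expressed in per cent, which may be why they were grouped. Only the first is a proportion of units with a binary status.

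**3. What a cut-off would do.** Let a and s be one patient's percentages with the anti-reflux and the standard catheter, and c a cut-off. The pair is discordant, and so counts in McNemar's test, only if c falls between a and s. A pair with both values on the same side of c contributes nothing, however far apart the values are. The counted pairs therefore change with c, and each keeps only the direction of its difference.

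The exact two-sided p value when all d discordant pairs point the same way is 2 × 0.5^d:

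- d = 5: 2 × 0.5⁵ = 0.0625
- d = 6: 2 × 0.5⁶ = 0.031

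At least 6 discordant pairs among the 25 patients are thus needed before significance at 0.05 is possible.

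**4. Illustration under assumed values.** The documents give no figures for this endpoint, so all inputs here are assumptions. There are 25 pairs, a standard-catheter mean of 92%, a between-patient SD of 4 points, values capped at 100%, the exact McNemar test at two-sided 0.05, and 4,000 simulated trials per setting. The SD of the difference is stated before capping.

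| Mean gain / SD of difference (points) | Paired t | McNemar, cut-off 85 | 90 | 95 | 98 |
|---|---|---|---|---|---|
| 3 / 5 | 79% | 1% | 24% | 31% | 17% |
| 3 / 6 | 64% | 2% | 22% | 24% | 16% |
| 5 / 8 | 81% | 8% | 38% | 47% | 41% |

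In each row the power of McNemar's test varies widely with the cut-off and stays below that of the paired t test. The levels depend on the assumptions.

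**5. The denominator.** Let P be the prepared activity, C the calculated activity and R the residual. Outcome assessment gives (P − R)/P. Study objectives, read literally, gives (P − R)/C, which equals the former multiplied by P/C. The two agree only when P = C. The article neither states that they are equal nor gives a typical P/C.

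**The case against.** The strongest reply is that this is a condensed article. McNemar's test is valid for a percentage split at a threshold fixed in advance, and such a threshold could stand in the full protocol or analysis plan. This stands in part. A reader might infer that the test can never be applied, or that a threshold would have to be invented once the data are seen. The article supports neither. It does support a narrower statement: the definition and the analysis class it prints do not match, and it prints no threshold to reconcile them. That is a conflict between two things stated, not an omission left to another document.

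A reader might also infer that nearly all infusions will be close to complete, so that discordant pairs will be too few for significance. Nothing in the article gives an expected efficiency for either catheter. The minimum of 6 discordant pairs is a property of the test and applies equally to disease control, for which the test is appropriate. The power figures above show dependence on the cut-off; they are not a forecast for this trial.

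On the denominator, a reader might infer that preparation error contaminates the catheter comparison. That would follow only if the short description in Study objectives overrode Outcome assessment. The latter is the formal definition, and measuring residual activity in vial, lines and catheters suits the prepared activity. The discrepancy is one of wording.

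Finally, a rank test is not a necessary part of the remedy. The signed-rank test in its usual form drops zero differences, and the plan already assigns a paired t test to continuous outcomes.

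**Conclusion.** The mismatch is real and is settled by the text alone. Infusion efficiency is a continuous paired percentage, and the class and test assigned to it are for a binary outcome that the article does not define. Splitting the percentage would lose information and tie the result to the chosen cut-off. How much would be lost in this trial cannot be determined from the document.

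The importance is moderate: this should be fixed, but the trial does not hinge on it. The endpoint is secondary, the primary T/N comparison and the sample size are untouched, no stopping rule or interim analysis depends on it, and the raw percentages are measured in any case, so no data are lost. The calculated-versus-prepared difference is minor. The conclusion rests on the article as the only source; a pre-specified cut-off elsewhere would make the test usable, but the article would still need to state it.

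**What to change.** 1. In Statistical analysis, move infusion efficiency from the categorical to the continuous outcomes. Compare it with the paired t test already planned for them, and report the mean within-patient difference with a 95% confidence interval. A Wilcoxon signed-rank test may be named as an option if the differences are skewed.
2. Keep McNemar's test for disease control.
3. In Study objectives, replace calculated with prepared activity so that it agrees with the definition in Outcome assessment.
4. If a binary endpoint was in fact intended, state the cut-off and the reason for it before the data are analysed.

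The cost is about two sentences of wording. Measurements, procedures and sample size do not change.

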**Methods/Design:**

A within-patient randomized controlled trial (RCT) will be conducted in 25 patients with unresectable chemorefractory liver-dominant CRLM. Study participants will undergo a ^166^Ho scout dose procedure in the morning and a therapeutic procedure in the afternoon. The ARC will be randomly allocated to the left/right hepatic artery, and a standard microcatheter will be used in the contralateral artery. SPECT/CT imaging will be performed for quantitative analyses of the microsphere distribution directly after the scout and treatment procedure. Baseline and follow-up investigations include ^18^F-FDG-PET + liver CT, clinical and laboratory examinations. The primary endpoint is the comparison of tumor to non-tumor (T/N) activity ratio in both groups. Secondary endpoints include comparisons of mean absorbed dose in tumors and healthy liver tissue, infusion efficiency, the predictive value of ^166^Ho scout dose for tumor response. In the entire cohort, a dose-response relationship, clinical toxicity, and overall survival will be assessed. The sample was determined for the expectation that the ARC will increase the T/N ratio by 25 % (mean T/N ratio 2.0 vs. 1.6).

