## Methods

### Hypothesis

We hypothesize that the use of the ARC increases the posttreatment T/N activity ratio and improves the predictive value of ^166^Ho scout dose distribution, in comparison with the use of a standard microcatheter (SMC).

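### The hypothesis that the ARC makes the scout dose more predictive than the SMC is analysed only by separate per-catheter summaries, with no ARC–SMC contrast or interval

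*Protocol article*

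**What the plan says.** The Hypothesis section of the protocol article has two parts. The second is that the ARC "improves the predictive value of ^166^Ho scout dose distribution, in comparison with the use of a standard microcatheter (SMC"). Study objectives repeats the comparative framing: "Secondary objectives include comparison of the following endpoints between administrations with the ARC and SMC", and the list that follows includes the "predictive value of the ^166^Ho scout dose distribution, and posttreatment tumor response".

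Outcome assessment defines the quantity: "The predictive value of the scout dose will be assessed by comparison of the distribution of the scout dose with the treatment dose". It adds: "The analysis will be based on tumor and healthy liver absorbed doses on SPECT/CT analysis". No per-territory measure of discrepancy is defined.

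Statistical analysis assigns a paired t test to continuous outcomes compared between ARC and SMC infusions (two examples are named) and McNemar's test to categorical ones. The scout dose is handled in separate sentences: the value of the "scout dose distribution will be assessed per catheter type", with correlation described by R² from linear regression and agreement by Bland-Altman limits.

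**The concern.** The question concerns a difference between catheters, while the named analysis describes each catheter alone. Followed as written, it produces one R² and one pair of limits for the ARC and the same for the SMC. Nothing in it estimates how much better the ARC predicts, or how uncertain that difference is.

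This is one of only two stated hypotheses. Each patient contributes both catheters, which is the main strength of the design, and for this hypothesis that strength is unused. A conclusion that the ARC does, or does not, make the scout dose more predictive would have to be drawn from two imprecise sets of figures placed side by side.

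**Working it through.** **Plan's own figure.** The article gives no sample size, effect size or precision for scout prediction. Its one calculation (23 patients, rounded to 25) concerns the T/N ratio. With a difference of 0.4 and 0.57 taken as the SD of the paired differences, noncentral-t power is 0.895 at 23 and 0.920 at 25. That agrees closely with the stated figure but has no bearing on the second hypothesis. Only n = 25 is carried forward, that is, 25 territories per catheter.

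**Step 1: do the named methods contain a contrast?**
- Hypothesis and Study objectives: ARC against SMC.
- Outcome assessment: scout against therapy.
- Statistical analysis, scout sentences: scout against therapy, separately by catheter.

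R² and the width of the limits of agreement are each a single number per catheter. There is no per-patient value to pair, so the paired t test named earlier in the section cannot be applied to them. It could be applied to the signed scout–therapy differences behind the Bland-Altman plot, but it would then compare mean bias. Two catheters with equal mean bias and very different scatter would look alike, although scatter is central to prediction.

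**Step 2: how precise is each summary at n = 25?**

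Fisher z for R²: z = atanh(r), with 95% limits z ± 1.96/√(25 − 3) = z ± 0.418.
- r = 0.9 (R² = 0.81): 1.472 ± 0.418 gives r from 0.783 to 0.955, so R² from 0.61 to 0.91.
- r = 0.8 (R² = 0.64): 1.099 ± 0.418 gives r from 0.592 to 0.908, so R² from 0.35 to 0.82.

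The two intervals overlap widely. These r values are illustrative; the article gives none.

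Each limit of agreement, in units of the SD of the differences, has a 95% half-width of about 1.96·√(1/25 + 1.96²/(2·24)) = 1.96·√(0.040 + 0.080) = 0.68.

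**Step 3: what could a paired contrast detect?**

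Let e be the scout–therapy discrepancy in a territory. The Pitman-Morgan test compares the SD of e between paired arms by correlating the within-patient sum and difference of the two e values, with t = r·√(23/(1 − r²)) on 23 degrees of freedom. Simulated power is below (20,000 replicates per cell, normal data, two-sided 0.05). The range covers correlation between the two lobes of 0 to 0.5. The SD ratios are assumptions, as the article states no target.

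| SD ratio, SMC/ARC | Power |
|---|---|
| 1.25 | 0.18–0.23 |
| 1.5 | 0.49–0.60 |
| 1.75 | 0.76–0.86 |
| 2.0 | 0.91–0.96 |

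Under a ratio of 1 the rejection rate was 0.048 to 0.050, so the test holds its level.

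A Fisher-z comparison of two R² values, treating lobes as independent, has power of about 0.24 for 0.64 against 0.81: (1.472 − 1.099)/√(2/22) = 1.24, and Φ(1.24 − 1.96) ≈ 0.24.

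**The case against.** The strongest reply is that this is a condensed article. The paired-t sentence is open-ended, a per-territory scout–therapy difference is a continuous outcome it might cover, and the exact contrast for a secondary endpoint is often left to the analysis plan, which is not shown. With 25 patients and power planned only for T/N, descriptive reporting is also defensible. Part of this stands: it limits the weight of the point and argues for an interval rather than a test. It does not remove the mismatch. The article does specify a method for this endpoint, and that method lacks the comparison its own hypothesis and objectives promise.

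Four stronger readings are tempting and not supported.
- **That the trial cannot answer the question.** The same catheter type is used on the same side at both procedures, so every patient with both procedures supplies a scout–therapy pair for each catheter. The gap is in the analysis, not the design.
- **That the Bland-Altman analysis would be meaningless because scout and therapy activities differ greatly.** This presumes unscaled doses. Outcome assessment says the analysis rests on absorbed doses and does not say they are left unscaled; it also speaks of comparing distributions. Putting a size on the effect would further need a liver weight that the article does not give.
- **That chance variation between two SDs can be read from an independent-samples F ratio.** The arms are paired, so that figure does not apply.
- **That the abstract's wording, predictive value of the "scout dose for tumor response", is part of this defect.** It does differ from the Outcome assessment, which concerns prediction of the therapy distribution, but that is a separate wording correction.

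**Conclusion.** The point holds as a mismatch between the stated question and the stated analysis. As written, Statistical analysis gives no estimate of the ARC–SMC difference in scout predictive value, no uncertainty for it, and no use of the pairing. Setting the per-catheter summaries side by side could not by itself separate the catheters unless the difference were large.

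The consequence is confined to one hypothesis on a secondary endpoint. It warrants correction, but it does not touch the primary T/N comparison. The precision figures assume 25 evaluable pairs, approximate normality and illustrative values of R² and SD ratio. Fewer evaluable pairs would widen every interval.

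**What to change.** In Statistical analysis:

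1. For each perfusion territory, and separately for tumour and healthy liver, define e = log(therapy absorbed dose ÷ scout absorbed dose scaled by administered activity). The scaling multiplies the scout dose by the ratio of therapy to scout activity in that territory. State how the scout activity per territory is obtained, since the article does not say how it is divided between the two sides.
2. Compare |e| between ARC and SMC within patients by a paired analysis, and report the difference with a 95% CI.
3. Optionally, compare the paired variances of e by the Pitman-Morgan test, or give a patient-level bootstrap interval for the difference in R² or in the width of the limits of agreement.
4. Keep R² and Bland-Altman limits per catheter as description, on the same activity-scaled scale.

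The cost is a few sentences and a little more analysis, using the SPECT/CT scans already planned. The limitation is power: with 25 pairs only about a 1.75- to 2-fold SD ratio would be found reliably. The text should therefore say that the interval is the main result and that a non-significant difference is not evidence of equal predictive value.

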### Study design

The SIM trial is a single-center, open-label, phase II, within-patient randomized controlled trial (RCT). As opposed to a conventional RCT design, patients act as their own controls; liver lobes (right versus left lobe) are the experimental units in this study. Patients with bilateral, irresectable, chemorefractory, liver-dominant CRLM will undergo two sequential procedures on the same day, during which a scout dose and a therapy dose of ^166^Ho microspheres will be administered in the left and right hepatic artery. These separate injections can be regarded as two separate treatments of functionally independent liver lobes. The use of the ARC will be randomly allocated (1:1) to the left or right functional liver lobe and a standard microcatheter (SMC) will be used in the contralateral side. The same catheter type will be used on the same side during the scout and therapy procedures.

This trial will be conducted in accordance with the principles outlined in the Declaration of Helsinki and will follow the Consolidated Standards of Reporting Trials (CONSORT) statement [10]. A Standard Protocol Items: Recommendations for Interventional Trials (SPIRIT) checklist is provided in Additional file 1 [11].

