#### Treatment planning

Eligible patients will be asked to provide informed consent to participate in the study. Next, the interventional radiologist and nuclear medicine physician will make an individualized treatment plan (including identification of the target vessels for selective infusion, identification of extrahepatic branches, and determining the need for coil embolization), based on the anatomy of the hepatic arterial vasculature visualized on pretreatment CT images. In all procedures, two selective injection positions (in the left and right hepatic artery) will be used to treat the whole liver on the same day. In patients with a variant hepatic arterial configuration, intrahepatic arterial branches (for example, the segment 4 artery) may be coil embolized to induce redistribution of blood flow through intrahepatic collaterals, and enable the use of two selective injection positions.

The total amount of ^166^Ho activity (A_Ho166_) required to deliver a whole liver absorbed dose of 60 Gy – the maximum tolerable radiation dose previously determined in a phase I dose-escalation study – is calculated using the formula:$$ {A}_{Ho166}(MBq)=\frac{60\;(Gy)}{15.87\;x\;{10}^{-3}\;\left(J/ MBq\right)}\;x\; Liver\; weight\;(Kg) $$Liver weight (in Kg) is determined by multiplying the volume of the liver (measurement based on CT) with the density of liver tissue (1.06 g/cm^3^). The scout procedure always consist of 250 MBq in 60 mg of microspheres (density 1.4 g/cm^3^), this activity is subtracted from the activity given in the treatment procedure. The treatment activity for each perfusion territory is fractionated based on its liver volume. If coil embolization of an intrahepatic branch is planned, the volume of its perfusion territory is included in the side that is anticipated to take over the blood supply.

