### Statistical considerations

#### Sample size calculation

A subgroup analysis of the T/N activity ratios in seven patients with CRLM, previously treated with ^166^Ho RE using a SMC [3], showed a mean T/N ratio of 1.6 (standard deviation 0.57). Sample size calculation, based on a two-sided paired *t* test for the comparison of T/N activity concentration ratios at an alpha level of 0.05 and power of 0.90, showed that at least 23 patients need to be included to detect a difference of 0.4 in mean T/N ratios (with an estimated standard deviation 0.57) in the ARC arm (estimated mean T/N ratio 2.0) and SMC arm (estimated mean T/N ratio 1.6). This corresponds to a 25 % increase (considered clinically relevant) in favor of the ARC arm. A rounded number of 25 patients will therefore be treated in this trial. Sample size calculations were performed with the computer program ‘PS: Power and Sample Size Calculation’ version 3.0 for MacOsX.

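### The dose-response regression pools two perfusion territories per patient with no term for patient, so its p values may be too small, and its linear form does not suit the CT response measures that the article defines

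*Protocol article*

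**What the plan says.** The Statistical analysis section gives one sentence on the method: "The dose-response relationship will be evaluated by linear regression analysis". Outcome assessment sets the variables and the unit: "The relationship between tumor absorbed dose on SPECT/CT and tumor response on both CT and" FDG-PET "will be characterized on the level of perfusion territories". Treatment planning fixes two territories per patient: "two selective injection positions (in the left and right hepatic artery) will be used to treat the whole liver on the same day". Sample size calculation gives the number of patients: "A rounded number of 25 patients will therefore be treated in this trial". The Abstract (Methods/Design) places the dose-response analysis in the entire cohort, so the ARC and SMC sides are pooled.

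Outcome assessment defines CT response in one way: "Response analysis will be performed in accordance with the Response Evaluation Criteria in Solid Tumors (RECIST) version 1.1", per functional lobe and summarised as a disease control rate. Metabolic response is the change in total lesion glycolysis from baseline. Study objectives lists dose-response among the secondary objectives. The two-sided 0.05 threshold is stated without restriction to any one analysis.

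**The concern.** Two territories in one patient share that patient's tumour biology and treatment history. Ordinary linear regression on all territories counts them as separate pieces of information. Where dose and response both run together within patient, the standard error of the slope is too small, the confidence interval too narrow, and a dose-response relation is declared too often at p < 0.05.

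The rest of the same section respects the pairing. Catheter comparisons use a paired t test or McNemar's test, and the scout-dose regression is done per catheter type, which leaves one territory per patient. The dose-response regression is the one that puts both territories of a patient into one model without saying how the pair is handled.

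A second, smaller matter is the CT outcome. The only CT measures defined are RECIST response and disease control, and the Statistical analysis section itself lists disease control as categorical. The only dose-response method named is linear regression.

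The result matters because the Discussion relies on a dose-response relation to argue that better T/N ratios should improve tumour response.

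**Working it through.** **The plan's own figure.** The article gives no sample size or power for the dose-response analysis. Its only computed figure is for the primary paired t test: difference 0.4, standard deviation 0.57 (taken here as that of the within-patient differences), two-sided alpha 0.05, power 0.90, at least 23 patients. The exact noncentral t calculation gives power 0.895 at n = 23 and 0.908 at n = 24, so the figure reproduces to within one patient. Nothing below changes it.

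**Inputs for the dose-response check.**
- Patients: 25 (Sample size calculation).
- Territories per patient: 2 (Treatment planning), so 25 × 2 = 50 observations.
- Model: ordinary linear regression, no patient term (Statistical analysis).
- Within-patient correlation of dose (ρx) and of response (ρy): not in the article. Assumed 0.3 to 0.7 each, with 0 and 0.9 as outer cases.

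**Formulas.** For pairs, the variance of the slope is inflated by about 1 + ρx·ρy, which cannot exceed 2. The effective number of territories is 50 / (1 + ρx·ρy). The proportion by which the standard error is too small is 1 − 1/r, where r is the true over the model-based standard error.

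**Results.** Simulation with no true dose effect, 25 pairs, 20,000 trials per setting, nominal two-sided 5%:

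| ρx / ρy | 1 + ρx·ρy | r (simulated) | SE too small by | Type I error | Effective territories |
|---|---|---|---|---|---|
| 0 / 0.7 | 1.00 | 0.998 | none | 5.0% | 50 |
| 0.3 / 0.3 | 1.09 | 1.040 | 3.8% | 6.1% | 45.9 |
| 0.5 / 0.5 | 1.25 | 1.111 | 10.0% | 7.8% | 40.0 |
| 0.7 / 0.7 | 1.49 | 1.227 | 18.5% | 11.2% | 33.6 |
| 0.9 / 0.9 | 1.81 | 1.369 | 27.0% | 15.5% | 27.6 |

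With either correlation at zero, every simulated type I error lay between 4.7% and 5.3%. A separate simulation of the equal-correlation cases gave 5.9%, 8.0% and 10.8% at 0.3, 0.5 and 0.7.

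**Effect of the catheter contrast.** Each patient receives one catheter on each side, and the trial hypothesises that the ARC raises tumour uptake. A systematic dose difference between sides makes the two doses of a pair less alike. Assuming a shift of 0.4 / 0.57 = 0.70 SD (borrowed from the T/N figures, since the article gives none for dose) and ρy from 0.3 to 0.7:
- ρx = 0: type I error 4.1% to 4.5%.
- ρx = 0.3: 5.5% to 6.4%, against 6.1% to 7.4% without the shift.
- ρx = 0.5: 6.1% to 7.8%, against 7.0% to 9.2% without the shift.

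**CT outcome.** No arithmetic applies. The change in total lesion glycolysis is continuous, so linear regression is suitable in form for PET. RECIST response and disease control are categories, so it is not suitable for those.

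**The case against.** The strongest reply is that this is a condensed article. Its one-sentence description does not say that territories are treated as independent, and the authors plainly know about the pairing: "patients act as their own controls; liver lobes (right versus left lobe) are the experimental units in this study". A patient effect may stand in a fuller document. That is fair as to intent, and it is why the point is not put as a claim that the p values are wrong. But the article does name a method and a unit, and that method applied to that unit has the weakness shown. The sentence "These separate injections can be regarded as two separate treatments of functionally independent liver lobes" does not help, because it describes how treatment is delivered and does not make the outcomes of two lobes in one patient statistically independent.

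Three stronger readings are tempting, and the documents do not support them.
- A reader might infer that the standard errors are certainly wrong. They are too small only if dose and response are both positively correlated within patient. The article gives neither correlation, and the catheter contrast pulls the error rate down, to slightly below 5% when the dose correlation is otherwise zero. The Discussion's account of marked differences between patients in T/N ratio (0.6 to 25.9) makes correlation plausible but does not measure it.
- A reader might cite the common 60 Gy whole-liver target as a source of within-patient correlation. The same target applies to every patient, so it adds no variation between patients and cannot create that correlation.
- A reader might infer that a RECIST category will be entered as a continuous outcome. The article does not say so. RECIST assessment also yields a percentage change in diameters, and disease control is assigned McNemar's test elsewhere in the section. What stands is that no CT outcome suited to linear regression is named.

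**Conclusion.** The point holds in conditional form. Linear regression on two pooled territories per patient, with no patient term, gives a type I error of about 6% to 11% and standard errors about 4% to 19% too small when both within-patient correlations lie between 0.3 and 0.7. These correlations are assumptions. With either at zero there is no distortion, and a within-patient catheter effect on dose reduces the inflation. The pairing issue applies to both the PET and the CT response; the mismatch of model and outcome applies to CT only. The objective is secondary, so this is a change that should be made but does not threaten the trial's main conclusion.

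**What to change.** Replace the sentence on dose-response in the Statistical analysis section so that it states three things.
- **Metabolic response:** the change in total lesion glycolysis is modelled on tumour absorbed dose in a linear mixed model with a random patient intercept, or by linear regression with patient-clustered standard errors and a small-sample correction, which 25 patients call for.
- **CT response:** the outcome is named. If it is the percentage change in the lesion-diameter sum, the same model serves. If it is RECIST category or disease control, an ordinal or logistic model that accounts for patient is used.
- **Unit:** the perfusion territory is kept, with patient as the cluster.

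The cost is a sentence or two of text and possibly a slightly wider confidence interval. No extra measurements or patients are needed.
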